## Abstract

**Background:**

The incidence of eating disorders (EDs) among adolescents has significantly increased since the beginning of the COVID-19 pandemic. Hybrid care, which combines web-based and in-person modalities, is a promising approach for adolescents with EDs but remains understudied in this population.

**Objective:**

We aimed to implement a novel hybrid (web-based and in-person) intensive ambulatory care program for youth and evaluate its feasibility, acceptability, and preliminary effectiveness.

**Methods:**

We will use a naturalistic pretest-posttest design to evaluate our proposed pilot Intensive Ambulatory Care Program (IACP). This novel type of day hospital care follows evidence-based principles and uses a family-centered, educational, and motivational approach. It will be tailored to the psychological needs of each participant and will be delivered in a hybrid format. A total of 100 participants meeting the DSM-5 (Diagnostic and Statistical Manual of Mental Disorders, Fifth Edition) criteria for EDs, aged 12-18 years, will be recruited over the 2-year trial period. We will examine recruitment, retention, and adhesion-to-protocol rates; participant and family satisfaction; and preliminary effectiveness using quantitative self-report questionnaires.

**Results:**

Rolling recruitment will take place from winter 2022 to fall 2023, during which time we expect to recruit approximately 80% (100/120) of eligible participants, retain at least 75% (75/100) of enrolled participants and have at least 70% (70/100) of enrolled participants complete at least one therapeutic session per week and all pre- and postintervention questionnaires. Data collection will occur concurrently. We base our recruitment and retention estimates on previous literature and consider that the highly flexible design of the IACP and the fact that no extra work will be required of individuals in the program to participate in the study, will lead to high levels of feasibility. We anticipate that participants and their families will be satisfied with both the program and hybrid delivery format. We expect that participation in the IACP will be associated with a medium effect size reduction in ED psychopathology from baseline to end of treatment. The data analysis and manuscript writing are expected to be completed by the summer of 2024.

**Conclusions:**

Given the high clinical burden associated with EDs, this study has the potential to fill an important research gap by testing the implementation of a novel hybrid mode of intervention. If feasible, acceptable, and effective, the IACP could lead to important improvements in health care services for adolescents with EDs.

**International Registered Report Identifier (IRRID):**

PRR1-10.2196/37420

## Introduction

### Burden of Eating Disorders

Eating disorders (EDs) are a group of serious and complex mental illnesses characterized by disturbed beliefs about body weight, shape, and image, in addition to maladaptive eating behaviors, including restriction, purging, and other methods of excessive compensation for caloric intake [1]. Although EDs can affect individuals of all ages, they often occur during adolescence [2-4]. Illness severity varies widely, and symptoms are highly heterogeneous. The negative consequences of these diseases include poor quality of life, impaired psychosocial functioning [5], psychiatric comorbidities [6], multisystemic medical complications, and mortality [7]. The treatment of EDs also varies widely. Hospitalization is generally reserved for patients at high medical or psychological risk who are unresponsive to other treatments, while ambulatory care is used for patients with less severe forms of illness [1].

### Day Treatment Programs for EDs

Day treatment programs provide patients with care on multiple days or hours per week, at an intensity that falls between hospitalization and ambulatory care [8]. This is important for patients with moderate to severe illness who either do not require hospitalization or who can benefit from step-down care after an inpatient hospitalization. The literature supports the use of day treatment programs, considering the limited benefits of extended hospitalization when compared with short hospitalization followed by prompt transition to ambulatory care [9]. The latter option may also reduce health care costs [10] and allow for a more rapid return to school and social functioning without affecting clinical outcomes [9]. Therapeutic approaches used in day programs vary but can be categorized as either family-focused [11-13] or nonfamily-focused [14-16] with most of the latter combining several modalities, including cognitive behavioral therapy, dialectical behavioral therapy, behavioral therapy, cognitive remediation therapy, and acceptance and commitment therapy, among others [8]. Short-term hospitalization followed by day program treatment for adolescents with AN is noninferior in terms of weight outcomes, 1-year rates of readmission, and ED symptoms when compared with continued inpatient treatment [17]. Similarly, several uncontrolled trials [18,19] and a systematic scoping review of the literature [8] suggest that day programs alone are effective in promoting weight gain for those who are underweight, decreasing ED and comorbid psychopathology, and improving psychosocial functioning and quality of life among individuals with moderate to severe ED symptoms.

Considering the high rates of comorbid mental health symptoms among youth with EDs [20], there is a need for integrated treatment strategies targeting both ED symptoms and psychiatric comorbidities. Day treatment programs may offer a unique opportunity to combine multiple treatment modalities because of their intermediate level of intensity and increased scheduling flexibility compared with inpatient treatment. In many cases, day treatment may also allow for the continuation of school and work-related activities. One example of this integrated approach, which included the addition of a self-esteem and social skills therapy group to a multidisciplinary ED day treatment program, effectively improved outcomes, such as happiness, satisfaction, and self-concept related to weight, shape, and others [21]. Day treatment programs may also be particularly amenable to personalized treatment plans given their flexibility, and some interventions that have used data-driven approaches to elaborate personalized plans have been found to be preliminarily feasible and acceptable [22,23].

### Web-Based Day Treatment Programs for EDs

The provision of day treatment remotely using technology has the potential to increase access to treatment by addressing barriers such as precautions for infection control (in the context of current or future pandemics) and geographic distance from urban centers (where in-person day treatment programs are typically delivered). However, the evaluation of web-based day treatment programs for youth with EDs has been identified as a research gap [24]. Limited evidence from a naturalistic study conducted during the COVID-19 pandemic to evaluate the experiences of youth transitioning from an in-person to a web-based day treatment program, suggests that this approach is acceptable for youth [25]. A recent scoping review [24] also found that therapy delivered via videoconference, including family-based treatment, cognitive behavioral therapy, and relapse prevention using the Maudsley Model of Anorexia Nervosa Treatment for Adults, may be effective in the ambulatory setting, although evidence was drawn from uncontrolled case reports, pilot trials, and feasibility trials.

In light of the increased need for services for adolescents with EDs [26-30] and the limited amount of empirical evidence for integrated treatment strategies combining in-person and web-based care for the treatment of pediatric EDs and comorbid psychopathologies, we are implementing and evaluating a pilot Intensive Ambulatory Care Program (IACP), a novel type of day treatment program. Our program will be tailored to the psychological needs of each participant and delivered in a hybrid format, both web-based and in-person. We describe the proposed intervention and methodology of a naturalistic study that will be used to evaluate its feasibility, acceptability, and preliminary effectiveness.

### Objectives and Hypotheses

The primary objective of this study is to describe the feasibility and acceptability of flexible, modular, and hybrid IACP for adolescents with EDs. Secondary aims include describing the baseline characteristics of the adolescents who enroll in the IACP, describing the preliminary effectiveness of the IACP for adolescents with EDs in an uncontrolled naturalistic setting, and describing the moderating role of age, ED diagnosis (eg, anorexia nervosa vs other ED diagnoses), length of illness, and level of attendance on clinical response to the IACP.

We hypothesize that recruiting and retaining participants in the IACP would be feasible and acceptable. We expect that participants will mostly present restrictive ED symptomatology, which is representative of the patient population seen in the ED clinic where the study will be conducted; participants will present comorbid symptomatology and ED-related behaviors, such as anxiety and depressive symptoms [31,32], high levels of affective reactivity [33] and perfectionism scores [34], poor coping [35] and self-esteem [36] skills, and high levels of social media use [37], as reported in the literature. We expect that participation in the IACP will be associated with a reduction in ED psychopathology, from baseline to the end of treatment, and that patient age, ED diagnosis, length of illness, family connectedness, and the number of hours of therapy attended will act as moderators of the preliminary effectiveness of the intervention. Although there is no consensus on moderators of treatment outcomes in the adolescent population, these moderators were chosen based on limited evidence from several reviews [8,38,39] that have identified individual, clinical, and family-related factors that are related to treatment response.

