### Intervention

The intervention uses a family-centered, educational, and motivational approach that is based on the biopsychosocial model of EDs as described in Aimé and Bégin [46]. This model theorizes that a combination of sociocultural, environmental, familial, and individual factors, in addition to biological predispositions, converge to contribute to both the development and maintenance of disturbed beliefs and behaviors that characterize EDs. The therapeutic and psychoeducational modules (Table 2) were created based on this theory [46] and on a variety of similar sources such as books by Daniel J Siegel on mindfulness and by Martha M Linehan on impulse control [47], on cognitive behavioral and psychoeducational activities that are carried out in numerous ED treatments (eg, an open letter to my anorexia, metaphors for change, etc), and on original material created in partnership with patients.

Each participant will have an individualized treatment plan combining one or more modules, which will be established based on the initial questionnaire evaluation results and discussions between the clinician, the participant, and their family. Modules on one or more of the following themes will be presented as follows: (1) EDs and related psychopathology; (2) mental health and emotional regulation; (3) stress and anxiety management; and (4) identity, relationships, and life cycle issues in adolescence. Parents will be invited to participate in interventions pertaining to the physical and psychological components of EDs, meal accompaniment, stress, anxiety, hyperactivity management, and family life.

The intake and evaluation process, which will guide the creation of an individual treatment plan, will take place over 1 week. Following this, the intervention will take place over 4 weeks, with the possibility of extending it by 2 weeks, based on a discussion with the clinical team and the participant’s individual needs and progress. The intervention will conclude with 1 week of feedback and evaluation. Overall, the programming will last for 6 to 8 weeks.

**Table 2 table2:** Overview of the 4 therapeutic modules and corresponding activities and interventions offered within the Intensive Ambulatory Care Program.

Module	Activities and interventions
EDs^a^ and related psychopathology	Virtual meal accompaniment Hyperactivity management ED recovery and sources of motivation Perfectionism Body image

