Mental health and emotion regulation	Recognizing emotions Emotion regulation Impulsivity and anger Suicidal and parasuicidal behaviors
Stress and anxiety management	Recognizing emotions Mindfulness Relaxation techniques Psychoeducation about stress
Identity, relationships, and lifecycle issues in adolescence	Changes during adolescence and fear of growing up Self-esteem and self-affirmation The influence of social media Relationships with parents and friends Communication

^a^ED: eating disorder.

The time commitment for program participants will be variable but will involve a minimum of two to three 60- to 90-minute sessions per week, including meal accompaniment and preparatory activities with the adolescent and at least one parent or guardian. This represents a total of approximately 3 to 4 hours of programing per week. This will be in addition to regular planned outpatient clinical appointments with doctors, psychologists, social workers, etc. which will be considered usual care and which are not part of the IACP.

The modules of the intervention will be delivered using various formats, including in-person and web-based individual meetings, in-person and web-based meetings with parents, web-based synchronous therapy activities (eg, relaxation or mindfulness) administered by clinicians, individual web-based asynchronous therapy activities completed alone by participants with web-based feedback provided by clinicians, web-based viewing of prerecorded informational videos, and participant and family completion of personal logbooks and assignments. Each module has a set format (eg, individual vs group; in-person vs web-based) and was developed by the clinical team based on clinical experience and relevant literature.

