### Statistical Analysis

Statistical analyses will be performed using SPSS version 27.0. Feasibility and acceptability will be analyzed by summarizing quantitative data from (1) clinician-reported recruitment rate, retention rate, and adherence to protocol using descriptive statistics; (2) weekly satisfaction surveys of individual and group activities; and (3) postintervention surveys of overall satisfaction and satisfaction with the web-based mode of intervention. Qualitative data from both the weekly and overall satisfaction surveys will be analyzed using conventional content analysis. Patient characteristics at baseline will be summarized using descriptive statistics.

The preliminary effectiveness of the IACP intervention will be examined using general linear mixed models, with changes in global EDE-A scores from baseline to the end of treatment as the primary outcome. Appropriate covariates (eg, number of attended sessions) and random factors (eg, therapist) may be added to the statistical model for exploratory analysis. Similar general linear mixed model analyses will be run for the secondary outcome measures (Table 3), comparing scores from the baseline to the end of treatment. Finally, general linear mixed models will also be used to study the moderating role of the level of attendance and other clinical and psychosocial factors such as age, length of illness, ED diagnosis (anorexia nervosa vs other types of ED), and family connectedness on the primary outcome (change in EDE-A scores from baseline to end of treatment).

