## Discussion

### Anticipated Outcomes

We anticipate that our study will demonstrate the feasibility of running an innovative hybrid (web-based and in-person) IACP for adolescents in a specialized ED clinic located in a tertiary care hospital in a large urban center. We also anticipate that the intervention will be acceptable to both participants and their parents. We anticipate that the intervention will lead to a reduction in ED psychopathology, and that greater levels of participation in the IACP will be associated with a greater reduction in symptoms. We anticipate that participants recruited to participate in the study will represent a subset of the youth population with EDs on the more severe end of the disease spectrum (as patients with less severe illnesses would be less likely to be referred to the specialized ED program by their treating physician). Therefore, we anticipate that most study participants will present with severe ED symptoms (as measured by the EDE-A), comorbid symptoms of anxiety and depression, and personality traits predisposing them to perfectionism and low self-esteem, as reported in the literature [106,107].

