### Conclusions

Given the high incidence of EDs in the adolescent population and the important physical, psychological, and social impacts of these illnesses, research on scalable and adaptable treatment programs is crucial. Evaluating the feasibility, acceptability, and effectiveness of intensive ambulatory treatment delivered in a hybrid model is in line with this objective. Furthermore, the intervention we describe, using a hybrid and family-focused modular approach that adapts treatment to individual participants, has seldom been described in the existing literature. Despite its limitations, the findings of this study will help evaluate and refine our hybrid (in-person and web-based) IACP in real-life practice. It will also allow us to gain a better understanding of which patients could benefit from it the most. It is our hope that our study may help inform and improve the care of patients with EDs, both in our center and in other centers worldwide.

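### Total hours attended are tested as a moderator of response, although the length of the programme is itself decided partly on the participant's progress

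*Protocol article*

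**What the plan says.** Objectives and Hypotheses names five expected moderators: age, diagnosis, length of illness, family connectedness, and hours attended ("the number of hours of therapy attended will act as moderators of the preliminary effectiveness of the intervention"). The aims paragraph of the same section calls the last of these the level of attendance.

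Statistical Analysis states that "general linear mixed models will also be used to study the moderating role of the level of attendance" and other factors on change in EDE-A from baseline to end of treatment. It also says of the effectiveness model: "Appropriate covariates (eg, number of attended sessions) and random factors (eg, therapist) may be added". That sentence goes on to limit such additions to exploratory analysis.

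The Intervention section sets 4 weeks of treatment, "with the possibility of extending it by 2 weeks, based on a discussion with the clinical team and the participant’s individual needs and progress". On intensity it says: "This represents a total of approximately 3 to 4 hours of programing per week".

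Anticipated Outcomes gives the expected direction: "greater levels of participation in the IACP will be associated with a greater reduction in symptoms". Conclusions says of the findings: "It will also allow us to gain a better understanding of which patients could benefit from it the most".

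Future Implications says that guidelines for choosing between the regular and the extended programme are still to be created. Strengths and Limitations mentions external confounders (changes in primary treatment, seasonality, external stressors), but not the link between progress and programme length.

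**The concern.** A moderator is ordinarily a characteristic fixed before treatment. Age, diagnosis and length of illness meet that description; hours attended do not. Total hours depend on how many weeks a participant was kept in the programme, and one stated ground for that decision is progress. Progress during treatment is an early reading of the response that the EDE-A measures at the end, so the explanatory variable is partly a consequence of the outcome.

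If extension tends to go to participants who are improving slowly, more hours will look unhelpful. If it tends to go to those who are doing well, more hours will look helpful. Either pattern can arise with no dose effect, so the article's directional expectation could be falsely confirmed or falsely refuted.

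The study also has one arm, with usual care running alongside. Attendance and the baseline factors can be shown to predict change, but not to modify a treatment effect. Change here also contains natural course and concurrent care.

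**Working it through.** No figure stated in the article is in dispute. The check has two parts.

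**1. What the extension adds to hours** (Intervention section)

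- Regular programme: 4 weeks × 3 to 4 h = 12 to 16 h.
- Extended programme: 6 weeks × 3 to 4 h = 18 to 24 h.
- Difference: 2 weeks × 3 to 4 h = 6 to 8 h, and 6/12 = 8/16 = 50%.

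Programme length can therefore be a large source of variation in total hours.

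**2. What this does to a test with no dose effect**

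Input from the article: 100 enrolled and up to 25% attrition, so n = 100 × 0.75 = 75.

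Assumptions, none of them given in the article:

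- 30% are extended.
- Attendance rate is uniform from 40% to 100% and unrelated to response.
- Progress seen during treatment correlates ρ with final improvement.
- Extension goes to those with the least visible progress. It is decided either wholly on progress, or half on progress and half on independent reasons.

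Model: total hours = weeks (4 or 6) × weekly hours × attendance rate. Improvement is generated with no dependence on hours. The test is the correlation of hours with improvement at two-sided P<.05. A simulation gave these false-positive rates for total hours:

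| Extension decided | Weekly hours | ρ = 0.3 | ρ = 0.5 | ρ = 0.7 |
|---|---|---|---|---|
| Wholly on progress | fixed | 22% | 55% | 86% |
| Half on progress | fixed | 13% | 29% | 50% |
| Half on progress | varying 2 to 7 h | 9% | 17% | 28% |

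- With ρ = 0, the rate is about 5%, which is nominal.
- The mean spurious correlation with improvement is negative here, because slow progress was assumed to lead to extension. If good progress leads to extension, the sign reverses and the size is the same.
- Attendance counted only over weeks 1 to 4 gives about 5% in every cell of the table, because the extension cannot enter it.

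**3. What the common window does not cure**

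The clean 5% depends on the assumption that attendance is unrelated to response. If the attendance rate itself correlates about 0.25 with response, the proportion attended is significant in nearly 60% of runs, still with no dose effect. In this model, hours in weeks 1 to 4 are a multiple of that proportion and behave the same way. The window removes the artefact of the extension rule; it does not make attendance a baseline variable.

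**The case against.** The strongest reply is that this is a secondary aim, worded as description in an uncontrolled naturalistic setting. The primary objective is feasibility and acceptability. The expectation in Anticipated Outcomes is already put as an association, and level of attendance could be defined as a rate in a fuller analysis plan. Much of this stands, and it limits the weight of the point. It does not remove it: the hypothesis names a number of hours, the example covariate is a number of sessions, and nothing in the article relates either to planned length.

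Four stronger readings are tempting, and the documents do not support them.

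- *Slow responders receive more hours.* The article names needs and progress but gives no direction. The guidelines are still to be written and could rest on baseline scores, as those for module selection will.
- *The false-positive rate is close to 90%.* The high figures need extension to follow progress closely and progress to track outcome strongly. Both are assumptions.
- *The primary effectiveness model is adjusted for sessions attended.* That covariate is optional and confined to exploratory analysis.
- *The proportion of sessions attended would be free of bias.* It looks clean only if attendance is unrelated to response. Participants doing badly may skip sessions, and the Population section discontinues the intervention for those who become medically unstable.

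Nor must the sentence in Conclusions be withdrawn. It is hedged, and a qualification is enough.

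**Conclusion.** The point holds in a limited form. Total hours or sessions attended are a post-baseline quantity, partly determined by response through the extension rule, and the article neither corrects for this nor acknowledges it. A test of total hours against change in EDE-A cannot separate dose from the decision to extend.

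The size and direction of the bias cannot be fixed from the documents. Under the assumptions listed (n = 75, 30% extended, ρ from 0.3 to 0.7), the false-positive rate runs from roughly 10% to 85%; it returns to about 5% if extension is unrelated to progress. The range illustrates what is possible and is not an estimate for this study.

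The consequence is confined to the attendance-response aim and to wording about moderation and who benefits. The feasibility and acceptability results and the overall pre-post comparison are not affected by this point.

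**What to change.** - In Objectives and Hypotheses and in Statistical Analysis, replace total hours or sessions by attendance over the 4-week window common to all participants: hours, or the proportion of scheduled sessions, in weeks 1 to 4.
- Report change in EDE-A separately for the regular and the extended programme, as description. Do not use programme length as an adjustment term, because it is itself partly determined by response.
- Describe attendance and the baseline factors as predictors of, or as associated with, change in EDE-A, rather than as moderators of effectiveness. Qualify the sentence in Conclusions on which patients could benefit most to match.
- State that early attendance is still post-baseline and may itself reflect response, so it supports association only.

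The cost is the redefinition of one variable, one descriptive breakdown and a more modest claim. Attendance in weeks 1 to 4 also leaves out any contribution of the extension weeks. Attendance and programme length should already be on record for the adherence measures, so no new data are needed. The extension rule is a clinical matter and is not judged here.

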### Study Design

This study will have a natural design. Therefore, all participants who consent to the trial will receive the same individualized treatment modality as part of the IACP. The study will be an uncontrolled, pre- and posttest trial (Figure 1), comparing measures collected at baseline to measures collected at the end of treatment within participants.

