This study has a few limitations. First, being a single-site study, recruitment will be limited to the number of patients receiving care at the study site, which may limit the final sample size and generalizability of our findings. However, it should be noted that the study will be conducted in the largest tertiary pediatric care hospital in Quebec, a Canadian province with a population of 8.5 million inhabitants. Therefore, the results of this study can be generalized to other sites in large North American urban centers. Second, the naturalistic trial design and individualized treatment approach will make it so that some of the analyses and conclusions may be impacted by external confounders (such as changes in primary treatment, seasonality, and external stressors). However, it will allow for a better understanding of the real-world feasibility and acceptability of this type of day treatment program for EDs in adolescents. Third, given the highly flexible and personalized nature of the IACP, it will not be possible to compare the feasibility and preliminary effectiveness of in-person vs web-based treatment modules. However, acceptability data (satisfaction questionnaires) may provide important clues to the participants’ appreciation of the in-person and web-based components of the program. Finally, the short duration of follow-up in this project will not allow for long-term assessment of the effectiveness of treatment in reducing ED symptomatology. Future work may include long-term follow-up of youth participating in the IACP, as well as more detailed analyses on the effectiveness of different components of the program (eg, in-person vs web-based modules).

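### A single-arm pre-post study can find predictors of change, but the protocol presents them as moderators of the IACP's effectiveness and as showing who could benefit most

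*Protocol article*

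**What the plan says.** All references are to the protocol article.

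- **Design.** Study Design: "The study will be an uncontrolled, pre- and posttest trial", "comparing measures collected at baseline to measures collected at the end of treatment within participants". Everyone who consents receives the IACP.
- **Concurrent care.** Intervention, on the programme's weekly hours: "This will be in addition to regular planned outpatient clinical appointments with doctors, psychologists, social workers, etc". These appointments are classed as usual care, outside the IACP.
- **Secondary aim.** Objectives and Hypotheses: "describing the moderating role of age, ED diagnosis (eg, anorexia nervosa vs other ED diagnoses), length of illness, and level of attendance on clinical response".
- **Hypothesis.** The same section expects that age, diagnosis, length of illness, family connectedness and hours of therapy attended "will act as moderators of the preliminary effectiveness of the intervention". The Methods Overview likewise speaks of moderators of the effect.
- **Analysis.** Statistical Analysis: "general linear mixed models will also be used to study the moderating role of the level of attendance and other clinical and psychosocial factors", with change in EDE-A score from baseline to end of treatment as the outcome.
- **Limitation.** Strengths and Limitations: "some of the analyses and conclusions may be impacted by external confounders". The examples given are changes in primary treatment, seasonality and outside stressors.
- **Conclusion.** Conclusions, after the limitations: "It will also allow us to gain a better understanding of which patients could benefit from it the most".

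**The concern.** The benefit of the IACP to a patient is the change with it minus the change that would have happened without it. A factor moderates effectiveness if that difference varies across its levels. With no untreated or usual-care group, the difference cannot be estimated at any level of any factor. The planned models can show only who changes more over the 6 to 8 weeks, for whatever reason.

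What is at stake is the interpretation of a secondary aim. A factor that only marks a better natural course, such as a shorter illness, could be reported as marking patients whom the IACP helps more.

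**Working it through.** **1. What the planned contrast contains.** For a factor with levels 1 and 0, write the mean EDE-A change at level g as

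D_g = N_g + R_g + U_g + T_g,

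where N is natural course, R regression to the mean, U response to usual care and T the IACP effect. The planned analysis estimates

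D_1 − D_0 = (N_1 − N_0) + (R_1 − R_0) + (U_1 − U_0) + (T_1 − T_0).

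Moderation of effectiveness is the last bracket alone. The study gives one observed quantity for four unknown differences. Adjusting for baseline EDE-A may reduce the R term, but it cannot supply the missing contrast.

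**2. Small example (all four changes are assumed).**

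| Group | Improvement, usual care only | Improvement, with IACP | IACP benefit |
|---|---|---|---|
| Short illness | 0.6 SD | 0.8 SD | 0.8 − 0.6 = 0.2 SD |
| Long illness | 0.2 SD | 0.4 SD | 0.4 − 0.2 = 0.2 SD |

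The benefit is equal, so there is no moderation. A single-arm study sees only the IACP column and finds 0.8 − 0.4 = 0.4 SD. All of that is the prognostic difference, 0.6 − 0.2 = 0.4 SD.

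**3. The protocol's own figure.** Power Calculations gives f² = 0.15, significance level 0.05, power 0.80 and 68 participants. That reproduces as a regression F test with two predictors: λ = 0.15 × 68 = 10.2 on 2 and 65 degrees of freedom, power 0.804. The number of predictors is inferred, because the section does not name the test. Since f² = R²/(1 − R²), a single factor with f² = 0.15 has R² = 0.15/1.15 = 0.130 and r = √0.130 = 0.36. This measures association with the outcome. It is not a difference between treated and untreated patients.

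**4. How often a purely prognostic factor would be called a moderator.**

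- Completers: 100 × (1 − 0.25) = 75, from the protocol's target and dropout assumption.
- IACP effect: zero in everyone.
- Model: change = r·m + √(1 − r²)·e, with m (the factor) and e independent standard normal.
- Single-arm test: correlation of m with change, two-sided 0.05. With two time points and complete pairs, this stands in for the factor-by-time term of the planned mixed model.
- Comparison: two arms of 38 and 37 with the same total of 75, testing the arm-by-factor interaction.
- 4,000 simulated trials for each r. The r values are assumptions.

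| r | Single arm: significant 'moderator' | Two arms: significant interaction |
|---|---|---|
| 0 | 5.1% | 5.5% |
| 0.2 | 40.6% | 5.0% |
| 0.3 | 75.9% | 4.6% |
| 0.36 | 90.3% | 5.4% |
| 0.5 | 99.4% | 5.1% |

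The single-arm test detects association with change correctly. The error lies in naming that association moderation of effectiveness.

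**5. Attendance.** Level of attendance, or hours of therapy, arises after baseline. Under Intervention, the two-week extension depends partly on the participant's progress, so the amount of therapy received can itself follow from response. It is neither a baseline moderator nor a baseline predictor.

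**The case against.** Much of this can be called terminology. The aim speaks of clinical response, the analysed outcome is openly pre-post change, the setting is described as uncontrolled and naturalistic, and participation is expected only to be associated with improvement. A careful reader can see which contrast is computed. That stands for the aim. It does not stand for the hypothesis, which refers to the intervention's effectiveness, for the Overview, which refers to moderators of the effect, or for the sentence in the Conclusions.

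It can also be said that the limitations already cover the point. They do so in part: changes in primary treatment are named, which bears on concurrent care. Natural course, regression to the mean and the moderator analysis are not named, and the who-benefits sentence follows the limitations unqualified.

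The magnitudes above rest on assumed values and do not show how large the prognostic component is in this trial. That is correct, and they are offered only as illustration.

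A reader might go further and infer that the study will produce wrong patient-selection conclusions or steer referral. The document does not support that. It plans no selection or referral rule based on the moderator results. The threshold scores and guidelines under Future Implications concern choice of modules and programme length. The sentence in the Conclusions is hedged, speaking of better understanding and of who could benefit. A factor found to predict change might also turn out to be a true moderator; this study cannot tell.

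**Conclusion.** The point holds in a limited form. The hypothesis about moderators of effectiveness and the statement about who could benefit most claim something this design cannot deliver. They are unsupported and could mislead; they are not shown to be false. This rests only on the absence of a comparator and the presence of usual care, both stated in the protocol.

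The size depends on how strongly each factor relates to change without the IACP, which the document does not give. Over assumed correlations of 0.2 to 0.5, with no IACP effect in anyone and 75 completers, a single prognostic factor would be labelled a moderator in about 41% to 99% of trials.

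Moderation is a secondary aim of a feasibility pilot. The primary objective, feasibility and acceptability, is untouched.

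**What to change.** - **Objectives and Hypotheses, Methods Overview, Statistical Analysis:** describe age, ED diagnosis, length of illness and baseline family connectedness as exploratory baseline predictors of EDE-A change during the programme. Baseline needs saying for family connectedness because Table 3 schedules it at both time points.
- **Same sections:** describe attendance or hours of therapy separately, as a post-baseline variable associated with change and not as a moderator or baseline predictor.
- **Conclusions:** replace the benefit statement with *which patients improve most while in the programme, to be tested as moderators in a controlled study*.
- **Strengths and Limitations:** add that, without a comparator, these associations cannot show who benefits from the IACP.

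No undertaking about patient selection is needed, since no such use is planned. Data collection, models and sample size need not change on this account. The cost is a less ambitious secondary claim.
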